#### Phase 2: Development of the Survey Questionnaire and Cognitive Interviews

Before the fieldwork in Laos, we developed baseline and endline survey questionnaires to measure primary and secondary outcomes, along with other relevant indicators. Measures of parental health literacy, parental confidence in navigating the health system, and parental confidence in interactions with health care providers were adapted from the Consumer Health Activation Index [12]. Measures related to sick children were adapted from the Integrated Management of Childhood Illnesses [13]. Additionally, measures on care utilization, care experience, expectations for health care quality, and quality of care were adapted from the People’s Voice Survey [14], which had previously been implemented in Laos in 2022 [2]. Once finalized, cognitive interviews were conducted with 5 VITERBI participants in Lao-Tai, the official language, using a combination of the “think-aloud” and “scripted probing” techniques [15]. These interviews helped identify suitable terminology for concepts such as parental health literacy, health system navigation, and confidence in interactions with care providers.

The primary outcome of the study will be based on participants’ responses to the following question, asked in both the baseline and endline surveys: “If your child is sick tomorrow with a mild fever of 38°C and cough, which hospital, clinic, or health center will you take your child to?” This question was developed in accordance with the Integrated Management of Childhood Illness guidelines [13], in which the described symptoms would be classified as nonsevere. We developed this measure specifically for this trial, guided by our theory of how the intervention might influence decision-making. We aimed to create a measure that captured intentions about where participants would seek care in a future scenario, as we anticipated that the information provided through the intervention could shape these intentions. We sought an outcome measure that could be collected from all participants without depending on recent health care utilization. For this reason, we chose this measure over alternatives such as “most recent facility visited” or “usual source of care.” Cognitive interviews and pilot surveys indicated that the measure performed well in terms of participant comprehension.

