Additionally, we plan to measure 6 secondary outcomes to explore further effects of the intervention. These relate to caregivers’ actual health care use over the past 3 months, including satisfaction with care received, frequency of health care service use, and changes in the facility used for their most recent visit. Additionally, the secondary measures capture whether caregivers selected health facilities based on online or digital information, whether they changed their preferred provider for urgent care, and their confidence in identifying the best facility for their children’s care. The secondary measures are presented in Textbox 1.

Secondary measures.
**1. Proportion of mothers satisfied with health care for their children during their most recent visit (time frame: 3 months)**
This secondary outcome measure captures mothers’ satisfaction with the health care facility visited most recently for care of their child under age 2 years. This measure will be available only for mothers who sought care for their child during the study period. It will be a binary variable, with satisfaction defined as responding “excellent” or “very good” (as opposed to “good,” “fair,” or “poor”) to the question: “How would you rate the overall quality of care you received?” referring to the most recent visit for their child under age 2 years within the past 3 months.

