**2. Number and type of health care providers used in the past 3 months (time frame: 3 months)**
This secondary outcome captures the number and types of providers (government health centers, government hospitals, private clinics, and private hospitals) visited by mothers for their children’s health care during the study period. Every 2 weeks, all enrolled participants will be asked via a mobile app: “Did you visit a health center, hospital, or clinic for your child in the last 2 weeks?” Participants who respond “yes” will be asked to complete an online survey about the visit, specifying the health facility they visited.
**3. Proportion of mothers who changed their most recently visited health care provider for children (time frame: 3 months)**
This secondary outcome measures the proportion of mothers who changed the health care facility they most recently visited for child care services between the baseline and endline surveys. This will be a binary variable and will be available only for caregivers who sought care during the 3 months preceding both the baseline and endline surveys.
**4. Proportion of mothers choosing the preferred facility for nonurgent care based on online or digital information sources (time frame: 3 months)**
This secondary outcome measures the proportion of mothers who used online or digital information sources to inform their choice of providers for nonurgent care. During the baseline and endline surveys, participants will be asked to specify their preferred location for nonurgent child care using the question: “If your child is sick tomorrow with a mild fever of 38°C and cough, which hospital, clinic, or health center would you take your child to?” Immediately following this, participants will be asked: “Was this choice informed by online or digital information services?” This outcome will be recorded as a binary variable.
**5. Proportion of mothers who changed their preferred health care provider for children for urgent care (time frame: 3 months)**

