### Statistical Analysis

We will use the STATA (StataCorp) statistical software package for all analyses. Descriptive statistics will first be used to assess differences between the intervention and control groups in terms of baseline characteristics and potential confounding variables. Missing covariates will be imputed as needed, and system use (including adherence to the intervention) will be measured through self-reports at endline. Differences between the intervention and control groups after the intervention will then be analyzed for both primary and secondary outcomes. Two-tailed *t* tests or ANOVA will be used for continuous variables, and chi-square tests will be used for binary outcome variables.

For our main analysis, differences between the 2 arms (participants who received provider information biweekly and those who received no information) will be assessed using regression models. Participants with missing outcome data will be excluded from the analysis, as we do not plan to impute outcomes. For missing baseline covariates, we will assume that the data are missing at random and conduct a complete-case analysis using only observations with complete data for the relevant variables. Additionally, we will perform multiple imputation to handle missing responses for baseline covariates.

Given that this is a randomized trial with individual-level randomization and a cross-sectional design, our primary analysis will compare outcomes between treatment arms using data measured at endline. Therefore, we do not anticipate issues related to clustering or intraindividual correlation in the analysis of primary outcome measures. Treatment effects for continuous outcomes will be estimated using linear regression with robust SEs to account for potential heteroskedasticity, using the following regression model:

*Y_i_* = *β*_0_ + *β*_1_*T_i_* + *e_i_*

where *Y_i_* is the outcome for individual *i*; *T_i_* is the indicator for the treatment group; *β*_0_ is the value of the control group; *β*_1_ is the estimated treatment effect; and *e_i_* is the error term. For binary outcomes, we will use the following regression model:

logit(*Y_i_*) = *β*_0_ + *β*_1_*T_i_* + *e_i_*

In secondary analyses, we will adjust for baseline covariates—including age, wealth status, educational level, ethnicity, and parental health literacy—to account for potential differences and address any imbalances between the treatment and control groups.

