## Discussion

### Anticipated Findings

This protocol describes a randomized controlled trial designed to test whether a demand-side intervention influences health facility choices among mothers in Vientiane capital. We will assess whether information about the quality of health care facilities—generated by study participants during the pilot and study periods—encourages mothers to change their preferred providers for nonurgent conditions. Additionally, we will assess whether the intervention leads to higher satisfaction with care at the most recently used facility and test our theory of change that mothers in the treatment group are more confident in their ability to identify the best place to seek care for sick children.

This protocol has several key strengths. It will contribute to the literature on how to “ignite demand” for high-quality care, as called for by the Lancet Commission on High-Quality Health Systems. This study is among the first published efforts to generate demand for high-quality care, providing evidence on how users of the health system can influence its quality. The results will apply to health conditions beyond the focus of this study—health care for children. The study is particularly relevant in Lao PDR, where the number of health care providers is rapidly growing, ranging from small primary health centers to large tertiary hospitals. The absence of effective gatekeeping allows people to seek care at any facility, including tertiary hospitals. Despite the growing care options, Laotians remain unsatisfied with the quality of care, with only 28% rating their usual health care provider as high quality. It is critical to understand and address sources of low-quality care, as low perceptions of care quality can lead people to forgo care or not adhere to medical advice [18].

A recent study highlighted that facility selection is influenced by factors such as illness severity, distance, technical skills and respectfulness of health care providers, cost, availability of equipment and medicines, waiting times, and informal payments [19]. Many of these factors, however, are not readily accessible or comparable across facilities, despite persistent dissatisfaction with care quality and untapped options. This study seeks to change the status quo by empowering patients with comparable information on health care quality across multiple facilities.

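### Satisfaction and changed-last-visit are compared only among mothers who sought care after randomisation, which allows selection bias if the ratings affect care-seeking

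*Protocol article*

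**What the plan says.** The analysis sets are fixed in the protocol article, Methods, Outcomes, Textbox 1. For measure 1 (satisfaction): "This measure will be available only for mothers who sought care for their child during the study period". Measure 3 (changed most recently visited facility) "will be available only for caregivers who sought care during the 3 months preceding both the baseline and endline surveys".

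The Statistical Analysis section adds: "Participants with missing outcome data will be excluded from the analysis, as we do not plan to impute outcomes". Binary outcomes are compared by a logistic model with treatment as the only term. Adjustment for age, wealth, education, ethnicity and parental health literacy is a secondary analysis.

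Patient satisfaction is part of the objective in the Abstract and of the hypothesis in the Introduction. Under Anticipated Findings the authors write: "we will assess whether the intervention leads to higher satisfaction with care at the most recently used facility". For the secondary outcomes as a group, the Outcomes section says: "we plan to measure 6 secondary outcomes to explore further effects of the intervention". Among these it names "frequency of health care service use". The Limitations section does not mention selection by care-seeking.

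**The concern.** Randomisation makes the two arms comparable as wholes. It does not guarantee that the mothers in each arm who later visit a facility are comparable. If being sent the ratings makes some mothers seek care who otherwise would not, or deters others, the care-seekers in the two arms are different mixtures of mothers. A difference in satisfaction could then arise from who sought care, with no mother better or worse satisfied because of the intervention.

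What is at stake is the conclusion on satisfaction, which the article treats as one of its two aims.

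**Working it through.** **1. Which condition comes after randomisation.** Measure 1 requires a visit during the study period, so the whole condition is post-randomisation. Measure 3 requires a visit before baseline and a visit before endline. The first is fixed before randomisation and does no harm; only the second matters.

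**2. Whether the plan allows care-seeking to respond to treatment.** It does, in two places. Frequency of use is one of the outcomes meant to explore effects of the intervention. Under Anticipated Findings the article also says that "low perceptions of care quality can lead people to forgo care or not adhere to medical advice", and the ratings are meant to change mothers' awareness of quality. Against this, the theory in the Introduction is mainly about where care is sought, not whether it is sought. The document does not settle the direction or size of any effect on care-seeking.

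**3. Size, under assumed rates.** The article gives no care-seeking rate and no power for these two outcomes, so there is no figure of its own to reproduce. Let c be the share of mothers who would seek care in either arm, pA the share of them satisfied, e the share who seek care only under the intervention, and pI the share of those satisfied. Nobody's satisfaction is changed by the intervention. Then:

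- control arm: pA
- intervention arm: (c × pA + e × pI) / (c + e)

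With c = 0.60 and pA = 0.30 (assumptions):

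| e | pI | Intervention arm | Apparent effect |
|---|---|---|---|
| 0.05 | 0.10 | (0.18 + 0.005)/0.65 = 28.5% | −1.5 points |
| 0.10 | 0.10 | (0.18 + 0.01)/0.70 = 27.1% | −2.9 points |
| 0.05 | 0.60 | (0.18 + 0.03)/0.65 = 32.3% | +2.3 points |
| 0.10 | 0.60 | (0.18 + 0.06)/0.70 = 34.3% | +4.3 points |

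**4. A second set of assumptions.** Take pA = 28%, borrowing the Introduction's figure for recent visits described as high quality, and 300 mothers per arm at endline (the Outcomes section expects 600 in total). With care-seeking at 50% in control and 60% in the intervention arm, and pI = 48%, the intervention arm shows (0.14 + 0.048)/0.60 = 31.3%. That is a spurious 3.3 points, and a two-sided 5% two-proportion test rejects about 10% of the time. Over c = 40% to 70%, e = 5 to 15 points and induced seekers differing by 20 to 30 points, the bias is 1.3 to 8.2 points and the rejection rate about 6% to 30%.

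**5. The no-bias case.** If e = 0 and the same kinds of mothers seek care in both arms, the formula returns pA in each arm and the bias is zero.

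**6. What other analyses show in the last row of the table.** Counting visited-and-satisfied among all mothers gives 0.60 × 0.30 = 18% against 0.18 + 0.06 = 24%. This is a valid randomised contrast, but all 6 points come from added use. Trimming the excess 10/70 of intervention-arm seekers gives satisfaction among the always-seekers between (0.24 − 0.10)/0.60 = 23.3% and 0.24/0.60 = 40.0%. That interval includes the true 30%.

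**The case against.** The strongest reply is that the bias is conditional. Listing use as an outcome shows that it will be measured, not that it will move, and the stated theory concerns choice of facility. That stands: a reader might infer that randomisation is broken for these outcomes, and the documents do not support this as a fact.

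Three further readings also go too far:

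- That the article makes causal claims on both outcomes. The explicit wording covers satisfaction only, and is itself put as a question to be assessed. Outcome 3 has only the general phrase about exploring effects.
- That the authors saw the selection problem for the primary outcome and ignored it here. Phase 2 says "We sought an outcome measure that could be collected from all participants without depending on recent health care utilization", which concerns availability of the measure; selection after randomisation is not mentioned.
- That the outcomes should be replaced. Satisfaction with a visit is undefined without a visit, and the article discloses this. A composite coding non-visitors as no would class mothers of healthy children with the dissatisfied. Comparing an actual visit with the hypothetical baseline preference would change what outcome 3 measures.

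The magnitudes are also modest. In the largest case of the table, 180 against 210 seekers give a standard error of about 4.7 points, so 4.3 points is under one standard error.

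Some of the remedy is already in hand, since visits are collected every two weeks in both arms for measure 2. Bounds could also sit in an analysis plan that is not shown. But the article itself fixes the population, the exclusion and the model, and does not link care-seeking by arm to the reading of outcomes 1 and 3. The planned covariate adjustment removes the selection only if those covariates capture everything that drives both care-seeking and the outcome.

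**Conclusion.** The point holds as a conditional risk to two secondary outcomes. Satisfaction, and the endline half of changed-last-visit, are compared among mothers selected by behaviour after randomisation, and the plan allows that this behaviour may respond to the intervention. If it does, the comparison alone does not support a causal reading for satisfaction. If it does not, there is no such bias.

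The size is 27% to 34% apparent satisfaction against 30%, or 1.3 to 8.2 points over the wider grid. All of this rests on assumed care-seeking and satisfaction rates, because the article gives none by arm. The primary outcome is asked of every mother regardless of use and is not touched.

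**What to change.** Keep outcomes 1 and 3 as defined, and add the following before the data are analysed by arm:

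1. Label both as estimated among care-seekers.
2. Report the proportion seeking care in each arm beside them. Equal proportions are reassuring but do not exclude a change in which mothers seek care.
3. For outcome 1, add a supportive analysis in all randomised mothers with endline data: visited a facility and rated the care in the top two categories, versus not. Show both components by arm.
4. If care-seeking differs by arm, give trimming bounds for outcomes 1 and 3, stating the assumption that the intervention moves care-seeking in one direction only.
5. Word the satisfaction conclusion under Anticipated Findings accordingly: a difference among care-seekers, read as an intervention effect only if care-seeking is similar or the bounds support it.

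Outcome 3 should not be replaced by a comparison with the hypothetical baseline preference.

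The cost is a little more analysis and no new data collection. The supportive composite mixes use with satisfaction, so it cannot stand alone.

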**2. Number and type of health care providers used in the past 3 months (time frame: 3 months)**
This secondary outcome captures the number and types of providers (government health centers, government hospitals, private clinics, and private hospitals) visited by mothers for their children’s health care during the study period. Every 2 weeks, all enrolled participants will be asked via a mobile app: “Did you visit a health center, hospital, or clinic for your child in the last 2 weeks?” Participants who respond “yes” will be asked to complete an online survey about the visit, specifying the health facility they visited.
**3. Proportion of mothers who changed their most recently visited health care provider for children (time frame: 3 months)**
This secondary outcome measures the proportion of mothers who changed the health care facility they most recently visited for child care services between the baseline and endline surveys. This will be a binary variable and will be available only for caregivers who sought care during the 3 months preceding both the baseline and endline surveys.
**4. Proportion of mothers choosing the preferred facility for nonurgent care based on online or digital information sources (time frame: 3 months)**
This secondary outcome measures the proportion of mothers who used online or digital information sources to inform their choice of providers for nonurgent care. During the baseline and endline surveys, participants will be asked to specify their preferred location for nonurgent child care using the question: “If your child is sick tomorrow with a mild fever of 38°C and cough, which hospital, clinic, or health center would you take your child to?” Immediately following this, participants will be asked: “Was this choice informed by online or digital information services?” This outcome will be recorded as a binary variable.
**5. Proportion of mothers who changed their preferred health care provider for children for urgent care (time frame: 3 months)**
This secondary outcome measures the proportion of mothers who changed their preferred health care facility for urgent child care services between the baseline and endline surveys. Urgent care is defined as a child presenting with a very high fever and a red rash covering the body. During the baseline and endline surveys, participants will be asked to specify their preferred location for urgent child care using the following question: “If your child is sick tomorrow with a very high fever of 39-40°C and a red rash covering their body, which hospital, clinic, or health center would you take your child to?”This outcome will be a binary variable indicating whether participants changed their preferred location for urgent care between the baseline and endline surveys.

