Following enrollment, all participants will be asked to rate or review the most recently visited health care facility every 2 weeks; these ratings will generate user scores for the website (intervention). Participants will receive a WhatsApp message from the study coordinator: “Did you visit a health center, hospital, or clinic for your child in the last 2 weeks?” Those who respond “yes” will receive a URL to a web-based survey, along with their study ID and the last 4 digits of their phone number. Before completing the survey, participants will be required to enter their study ID and the last 4 digits of their phone number. This step will help track survey completions and identify duplicate entries. Once the 2 fields are entered, participants will be asked to complete the survey by identifying the name of the health facility visited, rating the quality of care received, and providing any additional comments about their visit. The questions in the web-based survey are adapted from the People’s Voice Survey questionnaire [16], a mobile-based tool designed to capture patient experiences. All questions use multiple-choice response options and focus on participants’ most recent visit to a health care facility within the past 2 weeks. Participants are asked to assess the quality of care their child received by responding to the following items:

How would you rate the overall quality of care your child received?How would you rate the knowledge and skills of your provider?How would you rate the equipment and supplies available to the provider, such as medical equipment or access to laboratory tests?How would you rate the level of respect your provider showed you?How would you rate the amount of time you waited before being seen?How would you rate the courtesy and helpfulness of the health care facility staff, excluding your provider?How would you rate the cost of services?How would you rate the cleanliness of the facility?

For each question, participants will select one of the following response options: excellent, very good, good, fair, poor, “I do not know,” or “I refuse to answer.”

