The principal investigator will monitor survey entries weekly to ensure completeness and identify duplicate entries. In the case of duplicates, the most recent entry will be retained. If participants do not respond to the initial WhatsApp message or fail to complete the mobile survey, the study coordinator will make up to 5 attempts to contact them via WhatsApp and administer the survey over the call.

Average ratings for overall quality of care and for specific dimensions of care will be displayed on the web page, which is the main component of the intervention. The study coordinator will share the URL of the health facility ratings website with the intervention group biweekly via WhatsApp. The message will read: “Sabaidee, please click on the link to see ratings of hospitals, clinics, or health centers for health care for your children, and let us know if you have any questions or comments.” The control group will not receive any intervention. Given that all participants in the pilot study exchanged WhatsApp messages at least once per month, biweekly sharing of the intervention URL over 3 months is expected to provide sufficient exposure to the website for participants in the intervention group. Research staff will conduct endline surveys with all participants during in-person visits 3 months after the baseline survey.

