### Outcomes

Trial outcomes will be measured through the in-person endline survey. For the primary analysis, we will assess the proportion of mothers who changed their preferred health care facility for nonurgent child care services between the baseline and endline surveys. The null hypothesis is that there is no difference between the control and intervention groups. The alternative hypothesis is that there is a difference between the 2 groups. This hypothesis aligns with our study aims, as it examines whether the use of provider facility ratings influences caregivers to seek alternative sources of health care for their children. Our primary analysis is cross sectional; for the panel analysis using the care-seeking panel, observations will be clustered at the household level.

Nonurgent care is defined as a child presenting with a mild fever of 38°C accompanied by a cough. During the baseline and endline surveys, participants will be asked to specify their preferred location for child care using the following question: “If your child is sick tomorrow with a mild fever of 38°C Celsius and cough, which hospital, clinic, or health center would you take your child to?” The primary outcome will be a binary indicator reflecting whether participants changed their preferred location between baseline and endline.

We used the proportion of mothers who changed providers (n=26, 45%) for nonurgent care in a 6-week pilot study involving 58 participants. All participants in the pilot received the intervention—a web page of facility ratings. Eligible women will be randomly selected from the ongoing VITERBI study for enrollment, and recruitment will continue until we reach 660 participants, with 330 in each intervention arm, assuming 10% attrition. Enrolling 300 participants per intervention arm provides 90% power, with a 2-sided α of .05, to detect a 12-percentage-point change in health facility choice, assuming 80% follow-up. We will collect and analyze baseline and endline survey data from mothers enrolled in the study. We anticipate completing 600 endline surveys and analyzing this sample.

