### Ethics Considerations

This study was conducted in accordance with the Declaration of Helsinki and received ethics approval from the Ethikkommission Nordwest- und Zentralschweiz in Switzerland (approval ID AO_2023-00063) on September 8, 2023, and from the National Ethics Committee for Health Research (NECHR) in Lao PDR on February 6, 2024 (No. 16/NECHR). The research will adhere to the principles of the Helsinki Declaration, and any secondary use of the study data will undergo new ethical approvals.

All study participants provided informed written consent before taking part in any study procedures. They were informed that participation was voluntary, that they could withdraw at any time, and that withdrawal of consent would not affect their subsequent medical assistance or treatment. No financial compensation was provided for participation; however, a small gift of appreciation was offered upon successful completion of the endline survey.

The project included several steps to safeguard data privacy. First, deidentified survey responses (baseline, endline, and mobile) were stored on password-protected servers. Second, WhatsApp was used only as a communication channel with participants and not for any data collection purposes. Communication was managed by dedicated staff using a unique WhatsApp profile created specifically for the study. All exchanges via WhatsApp were protected by the platform’s default end-to-end encryption. Finally, to further minimize risks, WhatsApp records were deleted once participants had completed the endline survey.

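### Secondary measure 2 (number and type of providers used over 3 months) is sourced to biweekly forms that hold only the latest visit, so it undercounts use, and the Outcomes section names a different source.

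*Protocol article*

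**What the plan says.** Textbox 1 of the Protocol article introduces measure 2 thus: "This secondary outcome captures the number and types of providers", grouped as government health centers, government hospitals, private clinics and private hospitals, over the study period. The lead-in to Textbox 1 describes the same domain as how often services are used. The only source in the definition is the biweekly question put to all participants by mobile phone. Those who answer yes "will be asked to complete an online survey about the visit, specifying the health facility they visited".

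Study Procedures says that the questions in this form "focus on participants’ most recent visit to a health care facility within the past 2 weeks", and that the mother identifies the facility visited, in the singular. On repeated entries it says "In the case of duplicates, the most recent entry will be retained". Description of the Study Intervention fixes 12 weeks of participation and 6 survey rounds.

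The Outcomes section opens differently: "Trial outcomes will be measured through the in-person endline survey". Ethics Considerations adds that "WhatsApp was used only as a communication channel with participants and not for any data collection purposes" and that "WhatsApp records were deleted once participants had completed the endline survey".

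**The concern.** The outcome is a total over 3 months, but the form named as its source takes one facility per fortnight. If a mother takes her child to a clinic and then to a hospital within the same 2 weeks, only the hospital is entered. This lowers the number and can distort the type, because the last stop in a sequence is kept and the earlier one is lost. Movement between facilities is what the trial studies. No later analysis can recover a visit that was never recorded.

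The second problem is the source itself. A 3-month recall question at endline and a sum over fortnightly forms differ in recall period, in missing data and in the counts they give. Two analysts following the same article could build measure 2 from different data.

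The third problem is the zeros. The web form opens only after a yes, so a true zero for a round rests on a 'no' sent by WhatsApp. Data Management makes asking that question a main purpose of WhatsApp, while Ethics Considerations says that WhatsApp collects no data and that its records are deleted.

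**Working it through.** **1. The plan's own figure.** Description of the Study Intervention gives 12 weeks with a survey every 2 weeks: 12 / 2 = 6 rounds, as stated. With one facility per form, the ceiling is 6 entries per mother.

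**2. Loss from recording one visit per round.** The documents give no visit rate, so I assume one. Let visits be Poisson with mean m per 12 weeks, spread evenly, and let every round be answered. The chance of at least one visit in a round is 1 - exp(-m/6), so

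expected recorded visits = 6 × (1 - exp(-m/6)).

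| Assumed true mean m | Recorded | Lost |
|---|---|---|
| 0.5 | 0.48 | 4% |
| 1 | 0.92 | 8% |
| 2 | 1.70 | 15% |
| 3 | 2.36 | 21% |

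For example, at m = 2: exp(-1/3) = 0.7165; 6 × 0.2835 = 1.70; 1 - 1.70/2 = 15%.

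This counts visits, which fits the lead-in's description of the domain as frequency of use. The title of measure 2 speaks of providers. On that reading the loss should be smaller: a repeat visit to a facility already recorded loses nothing, and a facility missed in one round may appear in another.

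**3. The two statements of source.** The opening of Outcomes places trial outcomes in the endline survey without exception. Textbox 1 places measure 2 in the biweekly survey and does not mention endline. Both cannot hold for measure 2.

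**4. What happens to a 'no'.** Study Procedures distinguishes mothers who do not reply from those who do, and has the coordinator make up to 5 attempts to reach the former. Data Management lists responses to the baseline, endline and mobile-based surveys as stored under individual codes. It does not say whether a bare 'no' to the WhatsApp question counts as such a response. Ethics Considerations points away from that. So the field procedure separates 'no' from silence, but the article does not show that the distinction reaches the dataset.

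**5. What an arm difference would require.** It needs unequal response between arms and unanswered rounds counted as no visit. With m = 2 in both arms and assumed response of 90% and 80%, the recorded means would be 0.90 × 1.70 = 1.53 and 0.80 × 1.70 = 1.36, a ratio of 0.90/0.80 = 1.125 with no true difference. With equal response the ratio is 1. The documents state neither unequal response nor the zero rule.

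**The case against.** The strongest reply is that this is a modest measurement limit in one of six secondary outcomes. Six forms that each name a facility do yield providers and types. If visits are rare the loss is only a few percent, and with equal use and equal response it is the same in both arms. This stands as to size. It does not remove the undercount or the conflict over the source.

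A reader might infer that a mother with no visit cannot be told from one who did not reply. The documents do not support that. The question has its own 'no', and both Study Procedures and Attrition describe non-responders being identified and contacted. Whether a 'no' is stored may be settled in the full protocol, which is not shown. What remains is that the article's statements on WhatsApp sit badly with its use to ask this question.

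A reader might also infer that response alone will make the arms differ. Only the intervention arm receives the extra biweekly message with the link, so unequal response is conceivable. But follow-up is described for both arms, no rule counts an unanswered round as zero, and Statistical Analysis excludes participants with missing outcome data.

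On duplicates, the identity check in Study Procedures reads most naturally as catching repeat submissions of one form. Loss of a genuine second visit by this route is possible only because a duplicate is not defined.

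Finally, the section on questionnaire development says that the baseline and endline surveys were built to measure secondary as well as primary outcomes and that care utilization is covered. The endline form is an appendix that is not shown and may already hold the needed items. That would make the fix easier, but Textbox 1 would still need to say so.

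**Conclusion.** The point holds for secondary measure 2 only. As written, its named source records one facility per fortnight and at most 6 entries per mother, so use is undercounted. For visits, the loss is about 4-8% at 0.5-1 visit per 12 weeks, 15% at 2 and 21% at 3, under a Poisson model with assumed rates and full response. For distinct providers it should be smaller, by an amount that the documents do not allow one to calculate. The contradiction between the opening of Outcomes and Textbox 1 rests on the text alone and needs no assumption.

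Retention of 'no' replies is unclear. A difference between arms through unequal response is a risk to guard against, and the 1.125 ratio only illustrates what it would take. The primary outcome rests on the baseline and endline surveys and is not touched. The point should be corrected but does not threaten the trial's main conclusion.

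**What to change.** Reconcile the opening of Outcomes with Textbox 1 by naming one source for measure 2, the same in both arms, and state whether visits or distinct providers are counted.

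- **Endline source.** Ask at the in-person endline for the number of visits and each facility used in the past 3 months, and use the biweekly forms only to feed the website. This agrees with the opening of Outcomes and costs one or two items, or none if the endline form already has them. The downside is 3-month instead of 2-week recall.
- **Biweekly source.** Add an item listing all visits and facilities in the 2 weeks. Treat as duplicates only entries for the same visit. Store yes, no or no reply for each round in the study database before WhatsApp records are deleted, and correct the statement in Ethics Considerations to match. Do not count unanswered rounds as zero, and report response by arm.

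The article describes the trial as under way with rolling enrollment, so a form changed part-way would mix two measurements. If the items cannot be added for everyone, report measure 2 as facilities named at the latest visit in each answered round, and state the undercount as a limitation. That costs only wording.
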